#### **2.04 Studies done on screening for depression strategies / approaches.**

There is a limited number of trials done to identify approaches that could increase the detection of depression among high risk populations including PLHIV.

In a developed country one study focused on comparing routine screening with usual practice (clinical signs and symptoms) in the high risk groups (Romera et al., 2013) while another focused on increasing detection through the use of a depression sensitive electronic booking system among pregnant women (Carroll, et al, 2013).

The pragmatic cluster randomised trial by Romera et al (in Spain) randomised the health workers to the control and intervention group. The health workers delivering the intervention screened the patients thought to be at high risk for depression. “High risk” was defined as fulfilling at least one of the following: history of depression, somatic symptoms without any cause, psychological comorbidities or drug abuse, or chronic pain. These patients were

evaluated using two questions: “Over the past two weeks, have you felt down, depressed, or hopeless?” and “Over the past two weeks, have you felt little interest or pleasure in doing things?”. The patients were further evaluated using a diagnostic interview.

The control was subjected to usual clinical practice procedures. There were however unable to detect a difference in cases of depression detected. This was attributed to the failure of the intervention arm to adhere to the screening strategies.

A study done in a developing country in Africa (Kenya) focused on the training the health workers to equip them with skills and knowledge on depression. The patients from the intervention clinics were trained in diagnosis of mental health conditions and allowed to offer mental health services on a daily basis. This study however found no difference in cases of depression of mental health (including depression) detected between the control and intervention (Jenkins et al., 2013). This study didn't however describe the strategy used.

A prospective observational, quasi-experimental study done by Schumacher and colleagues in a cohort of HIV patients, routinely screened and followed patients for 4 to 6 months. The results obtained were compared against the baseline results. The study demonstrated routine screening for depression can not only identify patients with depression but also patients at risk of other psychiatric conditions. This study was done in the United States of America in a HIV clinic cohort. This study was however prone to confounding bias and the study focused on only one clinic.

There is however hardly any trial comparing selective to routine screening strategy. However, a number of studies done have focussed on the effect of notifying the health workers about the patient's depression risk status. In these studies, Patients with depression identified in clinics used to be randomised to either the intervention or control. The intervention arm was notified about the patients' depression risk status while the while the control was not. A meta-analysis

on the effects of notifying health workers on the patients' depression risk status showed that the case detection improved by a range of 10% to 20% (Pignone et al., 2002). However, these studies were done in developed countries among general patients not specifically the PLHIV. These studies however focussed on notification and not screening procedures. However, it is important to note that the study brings out the fact that frequent notification increases diagnosis and treatment of depression. A strategy that could therefore bring about more impressions of depression could be of benefit to the people of risk.

### **2.05 Perceptions of depression screening**

There is scarcity of literature on the perceptions of primary health workers on the screening for depression among PLHIV.

In the United States of America (USA), preventive task force recommends screening for depression in the general population of adults, including pregnant and postpartum females. The task force however recommended screening to be implemented with adequate systems in place to ensure accurate diagnosis, effective treatment, and appropriate follow-up. However, some countries such as the United Kingdom do not find it appropriate to screen for depression in the general population citing high false positives as the reason (USPTF, 2017).

In Africa, a study in Zimbabwe found the following issues critical and could interfere with the implementation of mental health care. These include: lack of training in mental health, low clinical staff levels, unavailability of psychiatric drugs, unavailability of time for counselling, and poor and unreliable referral systems for people suffering with depression (Chibanda et al., 2016). The shortcoming is however the absence of the viewpoints in the domains of self-efficacy (beliefs about capabilities), beliefs about consequences of screening (anticipated outcomes/ attitudes), memory / attention / decision process, social influences, emotions, behavioural regulation, and roles and identity of the health workers.

## **CHAPTER THREE**

### **3.00 METHODS**

#### **3.01 Study design**

A mixed methods study design with quantitative and qualitative data collection methods.

##### **Objective one**

A randomised controlled trial design will be used to determine whether there is a difference in cases of depression detected when using routine or selective screening strategies.

##### **Objective two**

A qualitative study employing key informant interviews among HIV health care providers.

#### **3.02 The study setting.**

The study setting is Princess Diana Memorial Health Centre IV is a government health facility found in Soroti district found in the north-east of Uganda. Soroti district has a population of 296,833. The prevalence of HIV in north-east Uganda is 3.7%. Princess Diana Memorial Health Centre IV is located in a peri-urban setting within northern division along Soroti-Moroto road. Northern division has a population of 19,382 (UBOS, 2014). Princess Diana Memorial Health Centre IV has a catchment population of approximately 11,500 people. The health unit has approximately 470 HIV positive patients with two clinic days per week with an attendance ranging from 20 to 35 patients per clinic day. The health centre is staffed with two psychiatric nurses serving the mental clinics in addition to the other non-psychiatric staff.

## **Methods for objective one**

In order to determine whether there is a difference in cases of depression detected when using routine or selective screening strategies among PLHIV, a randomised controlled trial will be used.

### **3.03 Population**

#### **Target population**

All PLHIV aged 18 years and above attending the HIV clinics in Soroti district.

#### **Accessible population**

PLHIV aged 18 years and above attending the HIV clinics in Princess Diana Memorial health centre IV site during the study period (January 2018 to March 2018).

#### **Study population**

### **3.04 Eligibility criteria**

#### **Inclusion criteria**

All PLHIV aged 18 years and above attending the HIV clinics in the study site during the study period and who consent to participate in the study.

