## OPERATIONAL DEFINITIONS

|                              |                                                                                                                                                                                                                                                                                                                                                                                                                                                            |
|------------------------------|------------------------------------------------------------------------------------------------------------------------------------------------------------------------------------------------------------------------------------------------------------------------------------------------------------------------------------------------------------------------------------------------------------------------------------------------------------|
| Depression            | 
Based on the PHQ-9 scores depression will be categorised as; scores of (0-4)-none, (5-9)-mild, (10-14)-moderate, (15-19)-moderately severe, and (20-27)-severe depression (Spitzer R, et al).
 
Based on the MINI; MDD, current, 5 or more answers (A1-A3) coded yes. MDD, recurrent (A4) coded yes (following diagnosis of major depressive disorder current ) (Sheehan DV & Lecrubier Y, 1992).
                     |
| Screening             | 
The presumptive identification of unrecognized cases of depression by the appropriate application of the PHQ2 and PHQ9, examinations, or the M.I.N.I.
                                                                                                                                                                                                                                                                                               |
| Routine screening     | 
Screening every PLHIV attending the HIV clinics at every visit using the PHQ-2 and PHQ-9.
                                                                                                                                                                                                                                                                                                                                                           |

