#### **Exclusion criteria**

PLHIV who are too ill to withstand the study procedures will be excluded from the study.

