### **3.08 Study variables**

#### **The intervention**

The intervention will be comprised of routine screening. In this strategy PLHIV who consent will be subjected to the PHQ-2 and if the patient has a value greater than or equal to 3 in the PHQ-2 the patient will be subjected to PHQ-9. After wards all patients will be subjected to the M.I.N.I to confirm cases of major depressive disorder (MDD), and to identify the missed cases of MDD. The M.I.N.I will be used to identify the actual number of cases of MDD in the group.

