#### **The control**

The control arm will provide the standard of care which is selective screening. A patient who consents to the study will be subjected to the PHQ2 and later (if  $PHQ2 \geq 3$ ) PHQ 9 when the clinician finds it appropriate especially at the crisis points in life in accordance with the ministry of health 2016 guidelines for prevention and treatment of HIV in Uganda. The clinician will require to indicate the reason for screening before screening for depression.

After wards all patients will be subjected to the M.I.N.I to confirm cases of major depressive disorder (MDD), and to identify the missed cases of MDD. The M.I.N.I will be used to identify the actual number of cases of MDD in the group.

The crisis points in life include: newly diagnosed with HIV or at disclosure of HIV status; occurrence of any physical illness, recognition of new symptoms / progression of disease or hospitalisation or diagnosis of AIDs; introduction to medication; death of a significant other; necessity of making end of life; and permanency planning decision, major life changes like child birth, pregnancy, loss of a job, and end of a relationship.

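### Already known or treated depression is not separated out, so a recognised case left un-screened in the selective arm counts as missed

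*Protocol*

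**What the plan says.** The Operational Definitions describe screening as "The presumptive identification of unrecognized cases of depression by the appropriate application of the PHQ2 and PHQ9", or by examinations or the M.I.N.I.

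Section 3.04 includes "All PLHIV aged 18 years and above attending the HIV clinics in the study site during the study period" who consent. Its single exclusion is that "PLHIV who are too ill to withstand the study procedures will be excluded from the study". Earlier or current depression is not mentioned there, nor among the potential confounders in 3.08.

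Section 3.08 describes the arms. For routine screening: "In this strategy PLHIV who consent will be subjected to the PHQ-2", followed by the PHQ-9 at a score of 3 or more. In the control arm the same tools are used "when the clinician finds it appropriate especially at the crisis points in life", and the clinician must give a reason for screening. A known depression diagnosis is not on the list of crisis points.

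All patients in both arms then have the M.I.N.I. Under Measurement of variables in 3.09, detection is by PHQ-2 and PHQ-9, and the M.I.N.I. supplies the denominator of cases present. The outcome named in 3.08 is the percentage of cases missed.

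**The concern.** The definition of screening and the rule for scoring a miss refer to different patients. The definition covers unrecognised cases only. The scoring covers every patient with current major depression, and an existing diagnosis earns no credit as detection.

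The mismatch can act differently in the two arms. The routine arm gives the PHQ-2 to everyone, so a known symptomatic case can be scored as detected. The selective arm leaves the PHQ to the clinician, so the same kind of patient can go un-screened and be scored as missed although the depression was already recognised. Randomisation balances the number of known cases on average. It does not remove a scoring error that depends on the arm. At stake is whether part of the difference between strategies reflects how recognised cases are handled rather than how well each strategy finds unrecognised ones.

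**Working it through.** **1. The plan's own figures (3.05).** p1 = 0.95 missed under selective screening; p2 = 0.95 − 0.95 × 0.1 = 0.855; planned difference 0.095.

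n = [1.96·√(2 × 0.95 × 0.05) + 1.282·√(0.95 × 0.05 + 0.855 × 0.145)]² / 0.095² = 142.74, so 143. Adding 29 gives 172 per group and 344 in total. This reproduces the protocol. The point does not depend on the sample size. The calculation supplies the yardstick of 9.5 points and a control-arm detection of 1 − 0.95 = 0.05.

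**2. Inputs for the shift.**
- s, the chance that a screened known case is detected: PHQ-2 sensitivity 0.829 × PHQ-9 sensitivity 0.916 (both from 2.02) = 0.759. Multiplying assumes the two tools err independently.
- k, the share of M.I.N.I.-positive patients already known or treated: not in the protocol; 5% and 10% are assumed for illustration.
- r, the share of known cases re-screened in the control arm: not in the protocol.
- D, the true difference in the missed proportion among unrecognised cases.

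**3. Formula.** A known case is missed with probability 1 − r·s in the control arm and 1 − s in the routine arm, a difference of s(1 − r). The observed difference is (1 − k)·D + k·s(1 − r), so

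shift = k·[s(1 − r) − D].

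**4. Results if no known case is re-screened in the control arm (r = 0).**

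| True difference D among unrecognised cases | Shift | k = 5% | k = 10% |
|---|---|---|---|
| 0 (no true difference) | 0.759k | 3.8 points | 7.6 points |
| 0.095 (planned) | (0.759 − 0.095)k = 0.664k | 3.3 points | 6.6 points |
| 0.759 − 0.05 = 0.709 (routine arm detects all cases at 0.759, control arm detects 5%) | 0.05k | 0.25 points | 0.5 points |

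**5. Results if every known case is re-screened (r = 1).** The shift is −k·D. At D = 0.095 that is −0.5 points for k = 5% and about −1.0 for k = 10%, so the sign reverses.

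**6. Where the sign changes.** The shift is zero when s(1 − r) = D. If the PHQ detects known and unrecognised cases equally well, and control clinicians screen a share u of unrecognised cases, then D = s(1 − u) and the sign changes at r = u. Known cases screened less often than unrecognised ones favour the routine arm; screened as often, there is no bias; screened more often, it reverses. At the planned D with s = 0.759 for known cases, the change comes at r = 1 − 0.095/0.759 = 0.87.

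**7. Scale in patients.** Section 1.00 gives major depression in 9% to 32% of PLHIV in the region. With 172 per arm that is 15.5 to 55.0 cases. One known case scored as missed moves the control percentage by about 1/55.0 = 1.8 to 1/15.5 = 6.5 points. At k = 5% one expects 0.8 to 2.8 such patients per arm.

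**The case against.** Several objections have force.

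**Re-screening is not ruled out.** The protocol nowhere says that control clinicians know earlier diagnoses or would withhold the PHQ. The crisis-point list is not exhaustive and includes new symptoms, and 1.02 says the national guideline also calls for screening when clinical features appear. Only a known case with current major depression enters the denominator, and such a patient may well be screened. A reader might infer that the plan necessarily favours routine screening. The documents do not support that, because the sign depends on r, which they do not give.

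**Known cases are probably few.** Section 1.00 says close to 100% of cases are missed in developing countries, 1.01 that depression is not routinely screened for, and 1.02 that current practice is opportunistic and mostly not followed up. A reader might infer k = 5% from the 95% assumed missed in 3.05. That figure is the assumed miss rate of selective screening, not one minus the share diagnosed before enrolment. Nor do the two psychiatric nurses in 3.02 show that HIV-clinic patients are under their care.

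**The largest shifts need an extreme case.** The 3.8 and 7.6 points hold only if there is no true difference, so they should not be set beside the planned 9.5. Even 3.3 and 6.6 imply that the routine arm detects 14.5% of unrecognised cases but 75.9% of known ones with the same tools. If it detects both equally, the shift is about 0.05k.

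**Enrolling all attenders is defensible.** Active depression that a strategy does not pick up at the visit could be called a miss whatever the history. But that is a different question from the one the protocol's own definition poses, and the protocol does not say which it intends.

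An analysis plan could add a sensitivity analysis. It could not reliably recover a history that was not recorded before allocation.

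**Conclusion.** The inconsistency is real and rests on the protocol's text: screening concerns unrecognised cases, while eligibility and the denominator include recognised ones, with detection credited only through the PHQ. A recognised case can therefore be scored as missed in one arm and detected in the other.

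The size is uncertain. With no re-screening of known cases in the control arm, the shift lies between about 0.05k and 0.76k, and is 0.66k at the planned difference. With frequent re-screening it disappears or slightly reverses. These results rest on assumed k and r and on independent errors of the PHQ-2 and PHQ-9. The point supports a cheap improvement to what is recorded and counted. It does not show that the comparison is biased by any particular amount, or that it must favour routine screening.

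**What to change.** - **At enrolment, before the envelope is opened:** record whether the patient has a current diagnosis of, or is under treatment for, depression. Take this from the clinic record where possible and do not pass it to the screening clinicians.
- **In 3.09 and 3.11:** base the main missed-case percentage on M.I.N.I.-positive patients without known diagnosis or treatment, in both numerator and denominator. Report the result in all participants as a sensitivity analysis.
- **Alternative:** exclude patients with known or treated depression in 3.04.

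The cost is one enrolment item and one or two sentences. The main comparison loses a few cases: with 15.5 to 55.0 cases per arm, about 0.8 to 2.8 at k = 5% and 1.5 to 5.5 at k = 10%. Asking patients directly carries a small risk of cueing them, and through them the control clinicians, which is why the clinic record is preferable.

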#### **Exclusion criteria**

PLHIV who are too ill to withstand the study procedures will be excluded from the study.

### **3.05 Sample size estimate**

The following formula will be used;  $n = [Z_{\alpha} \sqrt{2p_1(1-p_1)} - Z_{\beta} \sqrt{p_1(1-p_1) + p_2(1-p_2)}]^2 / (p_1 - p_2)^2$ , (Dawson & G Trapp, 2004) where 'n' is sample size per group 'Zα' is the critical value of the Normal distribution at 'α', 'Zβ' is the critical value of the Normal distribution at 'β' and 'p1' and 'p2' are the expected sample proportions of the two groups.

Assuming 95% of the cases of depression are missed in primary care practice by selective screening (Jenkins et al., 2013) and we would like to notice a 10% reduction in the cases missed (Pignone et al., 2002).

$$(P_1 - P_2) / P_1 = 0.1$$

$$P_2 = P_1 - (P_1 * 0.1)$$

$$P_2 = 0.95 - (0.95 * 0.1) = 0.855.$$

$$n = [Z_{\alpha} \sqrt{2p_1(1-p_1)} - Z_{\beta} \sqrt{p_1(1-p_1) + p_2(1-p_2)}]^2 / (p_1 - p_2)^2$$

$$n = [1.96 \sqrt{2 * 0.95(1-0.95)} - (-1.282) \sqrt{0.95(1-0.95) + 0.855(1-0.855)}]^2 / (0.95 - 0.855)^2$$

$n = 142.74 \sim 143$  PLHIV per group and 286 in two groups

Catering for non-response at 20% per group,

$$0.20 * 143 = 28.6 \sim 29.$$

Therefore, a total sample size of 344 patients will be enrolled for the study with 172 PLHIV per group.

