## **CHAPTER ONE**

### **1.00 Introduction**

Depression is the leading cause of disability worldwide with over 300 million people affected (4.4% of the world's population) (UN health agency, 2017). It is one of the most prevalent mental health comorbidities among People Living with Human Immunodeficiency Virus (PLHIV) (Benton, 2008; Okeke & Wagner, 2013), and it is 2 to 3 times more prevalent among PLHIV in Sub-Saharan Africa (SSA) (Charlotte, Dabis, & de Rekeneire, 2017). In 2016, there were 36.7 million PLHIV worldwide accounting for 0.8% of the world's population aged 15-49 years ("Fact sheet - AIDS epidemic status," 2016).

Major depression among PLHIV in the SSA region is estimated to range from 9% to 32% (Charlotte et al., 2017). This burden is in a population with approximately 25.5 million PLHIV ("Fact sheet - AIDS epidemic status," 2016) amounting to 4.2% of the population of the region aged 15-49 year ("WHO | (GHO) data," 2017).

Lack of screening and subsequent treatment for mental health disorders can affect general health, quality of life, adherence to antiretroviral therapy (ART) and retention into care (9) and therefore affecting most stages in the HIV cascade of care. Depression has been associated with treatment failure and the emanation of drug resistant HIV strains (Hartzell, Janke, & Weintrob, 2008) and it is partly attributed to poor adherence to ART (Gonzalez, Batchelder, Psaros, & Safren, 2011). Screening for, and treating depression has been found to improve health outcomes (Gaynes et al., 2015).

About 46% to 50% of cases of depression are missed in primary care settings in developed countries (Caballero et al., 2008) and close to 100% in developing countries (Abebaw, 2017; Jenkins et al., 2013; Udedi, 2014).

In Uganda, the prevalence of HIV stands at 6.2% (WHO, 2017b) but varies in different regions of the country from 8% to 46% (Akena, 2013; Nakimuli, 2011; Nakku, Kinyanda, & Hoskins, 2013).

Though the ability of the MOH recommended strategy of “selective screening” to detect depression cases is not known, selective screening for depression could offer an advantage of less time spent on screening for depression and less work load. However, selective screening for depression may leave other PLHIV with depression not diagnosed given that the criteria does not cover all the risk factors.

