## **2.02 Screening for depression**

Screening for depression is done through use of screening tools, history taking and examinations. A number of tools are used to screen for depression and this variability in the tools have partly contributed to the high variability in the prevalence of depression in various settings(Charlotte et al., 2017). Some of the tools include; the Mini International Neuropsychiatric Interview (M.I.N.I), the 2 and 9 item Patient health questionnaires (PHQ2 and PHQ9).

The M.I.N.I is a short diagnostic structured interview developed to explore 17 disorders according to Diagnostic and Statistical Manual (DSM)-III diagnostic criteria. It is fully structured to allow administration by non-specialized interviewers (Sheehan DV & Lecrubier Y, 1992).

The PHQ-9 is a 9-item self-rating scale evaluating the key symptoms of depression during the past two weeks. The total score ranges from 0 to 27 with five categories of severity: minimal (0–4), mild (5–9), moderate (10–14), moderately severe (15–19) and severe (20–27), which guide in grading depression (MOH Uganda, 2016). The tool has a sensitivity of 91.6%, and specificity of 81.2% (Akena, Joska, Obuku, & Stein, 2013)

The PHQ-2 tool is a shorter version of the PHQ-9. It contains the first two questions found in the PHQ-9. The PHQ-2 score ranges between 0–6 and those with a score equal or greater than 3 are further evaluated using the PHQ-9. The PHQ-2 has a sensitivity and specificity of 82.9% and 90% respectively at a score of 3 (Kroenke, 2003). The PHQs however is mainly recommended for people aged 12 years of age and above(University of Washington, 2017)

Other tools include the Centre for Epidemiologic Studies Depression Scale (CES-D); the Hopkins Symptom Checklist (HSCL), among others.

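### The planned routine-arm missed rate of 85.5% does not fit the protocol's own PHQ sensitivities for a fully screened arm, and the 95% for selective screening is weakly sourced

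*Protocol*

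**What the plan says.** Section 3.05 describes the two planning values as those that "are the expected sample proportions of the two groups". The first, p1, comes from "Assuming 95% of the cases of depression are missed in primary care practice by selective screening", with a Kenyan training trial as the source. The effect is worded as "we would like to notice a 10% reduction in the cases missed", which gives p2 as "0.95 - (0.95 * 0.1) = 0.855". The resulting 143 per group becomes 172 per group and 344 in total after a 20% allowance for non-response.

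Section 3.08 gives every consenting routine-arm patient the PHQ-2, and the PHQ-9 when the PHQ-2 score is 3 or more. In the control arm the same sequence is used only when the clinician finds it appropriate. Section 3.09 counts missed cases against the MINI.

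On test performance, section 2.02 states "The PHQ-2 has a sensitivity and specificity of 82.9% and 90% respectively at a score of 3" and, for the PHQ-9, "The tool has a sensitivity of 91.6%, and specificity of 81.2"%.

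On selective screening, section 1.00 says that the ability of the recommended strategy "to detect depression cases is not known". Section 2.04 says of the Kenyan trial that it did not "however describe the strategy used".

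**The concern.** A sample size is only as good as the two proportions put into it. Here one of them, the missed rate in the routine arm, can be checked against figures elsewhere in the protocol. An arm in which everyone is screened with tools of 83% and 92% sensitivity should not miss 85.5% of cases. The other proportion describes what control clinicians will do, and the protocol gives no data on that.

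At stake is the power statement. The planning contrast of 95% against 85.5% is not one that the described design would produce. It also hides the quantity that drives power: the share of depressed control patients whom the clinician decides to screen.

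**Working it through.** **1. The plan's own figure.** With p1 = 0.95, p2 = 0.855, z = 1.96 and 1.282, and the formula in section 3.05:

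n = [1.96 × √(2 × 0.95 × 0.05) + 1.282 × √(0.95 × 0.05 + 0.855 × 0.145)]² / 0.095² = [0.6041 + 0.5309]² / 0.009025 = 142.74.

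This reproduces the stated 142.74. The point here concerns the inputs, not the arithmetic.

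**2. Serial sensitivity S in the routine arm.** A case is detected only if both the PHQ-2 and the PHQ-9 are positive. Inputs are 0.829 and 0.916 (section 2.02).

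| Dependence between the tools | S | Missed, 1 − S |
|---|---|---|
| Lowest possible: 0.829 + 0.916 − 1 | 0.745 | 25.5% |
| Independent: 0.829 × 0.916 | 0.759 | 24.1% |
| Highest possible: the smaller of the two | 0.829 | 17.1% |

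**3. What 85.5% would need.** Either S = 1 − 0.855 = 0.145, or only 0.145/0.829 = 17% to 0.145/0.745 = 19% of routine-arm cases being screened. Section 3.08 screens all of them.

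**4. What 95% would need.** In the control arm, p1 = 1 − f × S, where f is the share of cases that the clinician screens. Setting p1 = 0.95 gives f = 0.05/0.829 = 6% to 0.05/0.745 = 7%. That is possible, but the protocol gives no value of f.

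**5. Dependence of the requirement on f.** With S = 0.759, a pooled two-proportion calculation at 90% power and two-sided 5% gives:

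| f (assumed) | Missed, selective | Missed, routine | MDD cases per arm |
|---|---|---|---|
| 0.50 | 62% | 24% | 34 |
| 0.75 | 43% | 24% | 128 |
| 0.80 | 39% | 24% | 196 |
| 0.90 | 32% | 24% | 731 |

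If selective screening did miss 95%, roughly 7 to 9 cases per arm would suffice.

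**6. Power for the fixed 344.** After 20% loss, 172 × 0.8 = 137.6 patients per arm remain. Section 1.01 gives a prevalence of 8% to 46%, which is 137.6 × 0.08 = 11 to 137.6 × 0.46 = 63 cases per arm. An assumed 20% gives 27.5, taken as 28. Exact power of the pooled Z-test of section 3.11, by enumerating the two binomial distributions with p2 = 0.241:

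| Cases per arm | p1 = 0.80 | 0.70 | 0.60 | 0.50 | 0.39 |
|---|---|---|---|---|---|
| 11 (8%) | 81% | 62% | 41% | 24% | 10% |
| 28 (20%, assumed) | 99% | 94% | 79% | 53% | 23% |
| 63 (46%) | >99% | >99% | 99% | 87% | 44% |

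Under S = 0.759, p1 = 0.50 corresponds to f = 0.50/0.759 = 66%, and p1 = 0.39 to f of about 80%.

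**The case against.** The strongest reply is that 10% is a minimum effect worth detecting, not a forecast. The wording about what the investigators would like to notice leans that way, and section 1.05 speaks of a reduction of at least 7.5%. A trial may properly be sized on a floor below the effect it expects. If p1 really were 0.95, a routine rate near 24% would give more power, not less. That last step is correct. But section 3.05 calls both values expected proportions, and although this is the legend of a formula, the floor is anchored next to 95%. It does not protect a 9.5-point gap where the routine arm would lie: a gap of 9.5 points above 24.1% needs 476 cases per arm at 90% power, and 143 give 43%.

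A reader might infer that the 95% also contradicts the sensitivities. It does not, since it depends on f. Nor does it contradict the statement that the yield is unknown: it is introduced as an assumption, and assuming a value for an unknown quantity is normal planning. Section 1.00 also says that nearly all cases are missed in primary care in developing countries, and section 1.02 calls current practice opportunistic. Both lend some support to a high value. What remains is weak attribution to a trial whose strategy the protocol says was not described.

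The sensitivities are themselves borrowed. They come from different cited studies, the 91.6% is given without a cut-off, and performance in this clinic may be lower. They rule out 85.5% in practice but do not establish 17% to 26% as fact.

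**Conclusion.** The point holds for p2. On the protocol's own figures the routine arm should miss about 17% to 26% of cases, against 85.5% planned. No dependence between the two tools closes that gap, and no plausible loss of performance does. For p1 the finding is one of sourcing only.

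The effect on sample size has no fixed direction. On these assumptions, 143 cases per arm would be far too many if clinicians screen few depressed control patients, and too few for 90% power once they screen about 76% or more (with S = 0.759).

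A reader might infer that 344 is nevertheless enough because the true contrast is large. The documents do not support that. They give no value of f, and the control triggers in section 3.08 include any physical illness, so a high share is possible. At 28 cases per arm, power runs from 99% to 23% as p1 falls from 0.80 to 0.39. Equally, the documents do not show that the trial must fail.

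The conclusion assumes that the cited sensitivities apply roughly to MINI-positive patients here and that routine-arm screening is carried out as described. That 143 counts cases but is enrolled as patients is a separate matter, relevant here only because the table is by cases.

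**What to change.** Rewrite the planning paragraph of section 3.05:

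- Set p2 = 1 − S, with S the serial PHQ-2/PHQ-9 sensitivity of about 0.745 to 0.829, labelled as an assumption from literature values.
- Set p1 = 1 − f × S, with f stated as unknown and shown over a wide range that includes values above two-thirds, so that p1 runs from about 0.39 to 0.95.
- Keep 95% only as a labelled assumption at one end of that range, and drop its attribution to selective screening in the Kenyan trial.
- Tabulate the power of the planned Z-test by f and by expected MINI-positive cases per arm over the 8% to 46% prevalence range. State the resulting power for the fixed 344 without claiming that it is adequate.

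The cost is one revised paragraph and a small table. The downside is that the 90% power implied by the current calculation may give way to a less favourable range.
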